## Abstract

**Background:**

Cardiac rehabilitation (CR) improves outcomes in patients with heart failure. However, data on CR efficacy in patients with acute decompensated heart failure is limited. This study is designed to assess the efficacy and safety of CR in patients hospitalized in cardiac intensive care unit (CICU) with acute decompensated heart failure (ADHF).

**Methods:**

This is a single-center, randomized controlled, single-blind clinical trial. A total of 120 participants hospitalized in CICU with ADHF will be randomly allocated in the ratio of 1:1 to two groups: CR group and control group. Participants will receive tailored and progressive CR intervention or attention control. The CR intervention include personalized breathing training, small muscle group resistance training, and aerobic endurance training based on the physical fitness assessment results. The subjects will receive the CR training for 5 days and will be followed up for 6 months. The primary endpoints are the score of the short physical performance battery (SPPB) and 6-month all-cause rehospitalization. The secondary endpoints include cardio-pulmonary function, activities of daily living (ADL), in-hospital mortality rate and 6-month all-cause mortality rate.

**Discussion:**

This randomized, controlled, clinical trial will assess whether CR improves physical function and reduces rehospitalization in patients hospitalized in CICU with ADHF. The results will provide further research-based evidence for the clinical application of CR in patients with ADHF.

**Trial Registration:**

Chinese Clinical Trial Registry ChiCTR2100050151. Registered on 19 August 2021.

## Introduction

Heart failure (HF) remains a major public health issue worldwide. The prevalence of HF still continues to raise due to a growing and aging population and improvements in the treatment of cardiovascular diseases (1). Acute decompensated heart failure (ADHF), defined as the new onset or worsening of symptoms and signs of HF, is one of the leading causes of hospitalization (2, 3). Despite the drugs and device-based therapy have substantially improved over recent decades, the mortality and rehospitalization rates are still high in patients with ADHF (4–6).

Impaired exercise capacity in patients with ADHF has detrimental effects on the health-related quality of life (QOL) and adverse outcomes (7). In recent decades, the physiological basis of exercise benefits was acknowledged, which led to the development of cardiac rehabilitation (CR) (8). There is solid evidence from numerous trials and meta-analyses that exercise-based CR improves cardiorespiratory function, exercise tolerance and QOL in patients with chronic HF (9, 10). Several studies showed a reduced rehospitalization after the setting of CR in patients with chronic HF (11, 12). Exercise-based CR is strongly recommended (Class I, Level A) to improve exercise capacity and QOL as well as reduce HF hospitalization in patients with chronic HF by the 2021 European Society of Cardiology (ESC) guidelines for the diagnosis and treatment of acute and chronic HF (13). However, data on the efficacy and safety of CR in hospitalized patients with ADHF is limited.

Recently, the REHAB-HF trial showed tailored rehabilitation intervention improved the physical function in old patients hospitalized with ADHF (14, 15). In REHAB-HF trial, patients admitted to the intensive care unit were excluded. However, the management of ADHF usually requires intensive care. We hypothesize early CR will improve physical function and reduce mortality and rehospitalization in patients who enter the cardiac intensive care unit (CICU) with ADHF. The Short Physical Performance Battery (SPPB) is a well-established tool to evaluate physical performance and has predictive value in hospitalization, disability and mortality in patients with HF (16, 17). Therefore, SPPB score will be used as one of the primary endpoints of this protocol. In addition, this trial will evaluate whether CR intervention would improve 6-month rehospitalization, cardio-pulmonary function, activities of daily living (ADL), in-hospital mortality rate and 6-month all-cause mortality rate among patients with ADHF admitted to CICU.

## Materials and Methods

### Study Design

This is a single-center, randomized controlled, single-blind clinical trial, which is designed to evaluate the efficacy and safety of CR in patients hospitalized in CICU with ADHF. This study protocol follows the principles of the Standard Protocol Items: Recommendations for Intervention Trials (SPIRIT) statement (18). This study has been approved by the Ethics Committee of Xiamen Cardiovascular Hospital of Xiamen University (approved number: 2021YLK6) and registered at Chinese Clinical Trial Registry (registration number: ChiCTR2100050151).

This study includes a 5-day intervention period and a 6-month follow-up period. A total of 120 patients hospitalized in CICU with ADHF will be randomly assigned to the two groups with a 1:1 ratio. Participants will receive tailored and progressive CR intervention or attention control. Clinical outcome evaluation will be conducted before and after intervention and at 6 months. The flow diagram of the study protocol is outlined in Figure 1.

**Figure 1 F1:**
[figure not shown]
Study design. CR, cardiac rehabilitation; PLR, passive leg raise; SPPB, short physical performance battery; ADL, activities of daily living.

### Participants

Participants will be recruited in the CICU of the Affiliated Cardiovascular Hospital of Xiamen University. Subjects hospitalized with ADHF will be screened according to the inclusion and exclusion criteria. The eligible subjects who agreed to participate in this study will be further determined by a cardiologist.

### Inclusion Criteria

(1) Age ≥ 18 years old;

(2) Acute decompensated heart failure was defined according to the “2021 ESC Guidelines for the diagnosis and treatment of acute and chronic heart failure” (13). Combined with symptoms, signs and laboratory results, and meet all the following conditions:

(2.1) At least one symptom was worsened from baseline: (a) dyspnea (dyspnea after exercising, paroxysmal nocturnal dyspnea or orthopnea), (b) venous congestion of systemic circulation (edema of lower extremities, liver congestion, ascites), and (c) tissue hypo-perfusion (oliguria or anuria, cold clammy limbs, consciousness disorder, hyper-lacticacidemia, or metabolic acidosis);

(2.2) At least one of the following signs of heart failure: (a) pulmonary edema on exam or by chest X ray, (b) Increased b-type natriuretic peptide or N-terminal prohormone BNP, and (c) abnormal cardiac structure and/or function by cardiac ultrasound;

(3) The symptoms and signs are consistent with acute decompensated heart failure judged by the investigator;

(4) Patients who have New York Heart Association Cardiac Function class III or IV symptoms at admission;

(5) Clinical stability has been achieved for 24 h after optimizing treatment;

(6) Patient was independent with basic activities of daily living including the ability to ambulate independently (with or without the use of an assistive device) prior to admission.

### Exclusion Criteria

(1) Acute coronary syndrome within 2 days; onset of chest pain within 8 h; or combined with mechanical complications;

(2) Fatal arrhythmia, high-grade atrioventricular block, new onset atrial fibrillation or atrial flutter;

(3) Severe aortic valve stenosis;

(4) Acute myocarditis, acute pericarditis, or acute infective endocarditis;

(5) Severe hypertrophic obstructive cardiomyopathy;

(6) Patients with chronic kidney disease stage 4 and 5 undergoing long-term hemodialysis or requiring long-term hemodialysis within the next 6 months;

(7) A recent embolism, atrium, or ventricular thrombosis, thrombophlebitis;

(8) Patients who require a pacemaker, implantable cardioverter defibrillator (ICD), or ventricular assist device, or those awaiting cardiac transplantation within the next 6 months;

(9) Those who had received standardized cardiac rehabilitation within the past 6 months;

(10) Severe cognitive impairment (MMSE ≤ 9 points);

(11) Inability or unwillingness to comply with the study requirements;

(12) Patients who dropped out or discharged during the study period.

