### Sample Size

According to the results of the previous study, the baseline SPPB sores was 6.0 ± 2.8 in CR group and 6.1 ± 2.6 in control group, the SPPB sores at 3 months was 8.3 ± 0.2 in CR group and 6.9 ± 0.2 in control group (14). To minimize both false positive and false negative errors, the type-I error rate (α) is set at 0.01 instead of 0.05 and the type-II error rate is set at 0.1 instead of 0.2. The sample size is calculated according to the following formula: *n* = 2σ^2^ × *f* (α,β)/(μ_1_-μ_2_)^2^ (19). The sample size of each group was estimated to be 44 per group. Taking approximate a 20% drop-off rate and a 7% missing rate into account, the final sample size was set to 60 per group. Therefore, a total of 120 subjects will be recruited in this study.

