### Outcomes

The outcomes will be assessed by independent researchers who have been trained before the study. The primary outcomes are the SPPB score and 6-month all-cause rehospitalization. The secondary outcomes include cardio-pulmonary function, activities of daily living (ADL), in-hospital mortality rate and 6-month all-cause mortality rate. Cardiac function indicators are as follow: 6-min walking test (6 MWT) before discharge, SV before discharge, EDFR, SVR, NYHA classification, biochemical markers of myocardial necrosis, N-terminal brain natriuretic peptide (NT-pro BNP), and left ventricular ejection fraction (LVEF). Pulmonary function indicators include 1 second rate of transfer/discharge (FEV1/FVC) and maximum ventilation volume per minute (MVV). In addition, we will evaluate the Short-Form 36-Item Health Survey (SF-36), psychological assessment, nutritional assessment and cardio-cerebrovascular events (Table 2).

**Table 2 T2:** The follow-up schedule.

	**Baseline**	**1 month**	**3 months**	**6 months**
Smoking	X			
Sports	X			
Participate in phase II cardiac rehabilitation				
Psychological assessment	X		X	X
Nutritional assessment	X	X		X
Rehospitalization				
Cardio-cerebrovascular events				
36-item short-form (SF-36)	X	X	X	

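### Exclusion criterion 12 excludes patients on events that happen only after enrolment, over an undefined study period, which risks selection bias in both primary comparisons

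*Protocol article*

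**What the plan says.** All references are to the protocol article.

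- **Exclusion Criteria, item 12:** "Patients who dropped out or discharged during the study period".
- **Study Design:** "This study includes a 5-day intervention period and a 6-month follow-up period". The same section randomises 120 patients 1:1 and places outcome evaluation before the intervention, after it and at 6 months.
- **Outcomes:** "The primary outcomes are the SPPB score and 6-month all-cause rehospitalization". Some secondary measures are tied to discharge: "6-min walking test (6 MWT) before discharge, SV before discharge".
- **Sample Size:** "The sample size of each group was estimated to be 44 per group", and then "Taking approximate a 20% drop-off rate and a 7% missing rate into account, the final sample size was set to 60 per group".
- **Intervention:** in the rehabilitation arm, exercise starts only once the passive leg raising (PLR) test is positive, and training is halted if any of several listed events occurs. The control arm has neither condition.
- **Data Analysis:** no analysis set is named.

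Nothing in the article limits item 12 to the time before randomisation, and nothing says that the patients it describes stay in follow-up or in the analysis.

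**The concern.** An eligibility criterion has to be decidable before randomisation. Item 12 is not, because a patient cannot have dropped out of, or been discharged during, a study not yet entered. The article describes no run-in, and item 11 already covers patients unable or unwilling to comply, so item 12 adds only post-enrolment events.

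A team that follows the item as printed would treat some randomised patients as ineligible after the fact. The groups compared would then be those who stayed, not those who were randomised. If the reasons for leaving differ between arms and are related to function or prognosis, both primary comparisons are biased. If follow-up also stops for these patients, the missing data may not be recoverable later. Patients who cannot tolerate training also bear directly on the trial's stated safety aim.

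**Working it through.** **1. The two readings of the study period.** The term is not defined. Study Design says only that the study includes a 5-day period and a 6-month period.

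- *Wide reading (5 days plus 6 months).* Rehospitalisation requires a prior discharge. Excluding everyone discharged in this period leaves only patients who die in hospital or are never discharged within 6 months. None of them can be rehospitalised, so the rule and the second primary endpoint cannot both stand.
- *Narrow reading (the 5 training days).* Rehospitalisation stays observable. The rule still removes patients on a post-randomisation event. Under Intervention, only the rehabilitation arm may have its start delayed by the PLR test, which leaves more time to be discharged before the programme is finished, and only that arm can have training halted. The number and kind of patients removed can therefore differ by arm.

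**2. The plan's own allowance for losses.** Inputs from Sample Size: 44 per group before inflation, 20% drop-off, 7% missing, 60 per group after inflation.

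- 44 / (1 − 0.27) = 60.3, or 44 / (0.80 × 0.93) = 59.1. The stated 60 is reproduced.
- 20% of 60 = 12 per group (24 of 120), leaving 48. With the 7% as well, 60 × 0.73 = 43.8, about 44 per group.

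The inflation keeps about 44 per group after losses. It protects precision only, since a selected 44 is as biased as a selected 60. The article does not say that the 20% are the patients meant in item 12, so 12 per group shows the scale of loss the plan expects and is not a count of item 12 exclusions.

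**3. How removal would turn into bias (illustration only).** None of the inputs below are in the document, except the 1.4-point SPPB difference.

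*Rehospitalisation.* Assume a true risk of 40% in both arms, so no effect. If a fraction r of an arm is removed and the removed patients have risk q, the observed risk is (0.40 − r·q) / (1 − r).

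| Removed, CR / control | Risk in removed, CR / control | Observed CR | Observed control | Spurious difference |
|---|---|---|---|---|
| 20% / 20% | 40% / 40% | 40% | 40% | 0 |
| 20% / 20% | 60% / 60% | 35% | 35% | 0 |
| 20% / 20% | 60% / 40% | 0.28/0.80 = 35% | 0.32/0.80 = 40% | −5 points |
| 30% / 10% | 60% / 60% | 0.22/0.70 = 31.4% | 0.34/0.90 = 37.8% | −6.3 points (before rounding) |
| 20% / 20% | 20% / 40% | 0.36/0.80 = 45% | 0.32/0.80 = 40% | +5 points |

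*SPPB.* Removing a fraction p of an arm whose mean lies d above the rest shifts that arm's mean by −p·d, so the difference between arms shifts by −(p_CR − p_control)·d.

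- Equal p and d in both arms: 0.
- p = 20% against 10%, d = 2: −0.10 × 2 = −0.2 points.
- p = 30% against 10%, d = 3: −0.20 × 3 = −0.6 points.
- If those removed score below the rest, d is negative and the sign reverses.

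For scale, Sample Size quotes 3-month SPPB means of 8.3 and 6.9 from the previous study, a difference of 1.4. The two non-zero shifts are 14% and 43% of that. The comparison is loose, because this trial assesses outcomes after the 5-day intervention and at 6 months.

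**The case against.** The strongest defence is that item 12 is a misplaced withdrawal rule. The article plans 6-month follow-up and a rehospitalisation endpoint throughout and schedules tests before discharge, so its authors plainly expect patients to be discharged. The sensible reading is then drop-out or discharge before the 5-day programme is complete. The item also does not say that data are deleted or follow-up stopped. Analysis sets are commonly left to a statistical analysis plan, and the flow diagram (Figure 1) is not shown.

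Much of this stands. A reader might infer that the trial excludes everyone who could be rehospitalised. The document does not support that as a settled fact, because the study period is undefined and the narrow reading is plausible. A reader might also infer from the 20% drop-off that removal under item 12 would be large, but the article does not connect the two, and early discharges may or may not be inside that 20%. Nor does the article say that patients discharged early are the best recovered, or who leaves and why.

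What does not stand is the conclusion that the text is harmless. The objection is to a rule that is printed, not to detail left out. An analysis plan that kept all randomised patients would contradict the item as written. A withdrawal rule that removes patients from the analysis has the same defect, and one that keeps them does not belong among the exclusions.

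**Conclusion.** The point holds as a faulty stated rule. Item 12 makes exclusion depend on post-enrolment events over an undefined period. On the wide reading it contradicts a primary endpoint, and on the narrow reading it removes patients on events that allocation can influence. Both primary comparisons are therefore at risk of selection bias.

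The size and sign of that bias cannot be derived from the document. It is zero if removal is unrelated to outcome, and in the examples above it also cancels when removal works identically in both arms. The differing conditions on training give no reason to rely on either. The figures of −0.2 to −0.6 SPPB points and −6.3 to +5 percentage points rest wholly on assumed inputs and are not estimates for this trial. That the analysed groups will in fact differ from the randomised groups is a risk created by the wording and is not established. The point still needs correcting, because it touches both primary endpoints and outcomes not collected from removed patients may be lost for good.

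**What to change.** 1. Delete item 12 from the exclusion criteria. If it was meant to concern training, restate it as discontinuation of training only, with no bearing on follow-up or analysis.
2. State that all 120 randomised patients are analysed in their assigned group, whatever training they received.
3. For patients leaving before day 5, in either arm, obtain the post-intervention SPPB at discharge.
4. Seek rehospitalisation and death to 6 months for every randomised patient, as far as consent allows.

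The cost is an amendment to the wording and a small number of SPPB assessments brought forward by the existing blinded assessors. No new sample size follows from this point. The downside is some dilution of the effect, because patients with little training stay in the rehabilitation arm, and a post-intervention SPPB taken earlier than day 5 in those who leave early.

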### Sample Size

According to the results of the previous study, the baseline SPPB sores was 6.0 ± 2.8 in CR group and 6.1 ± 2.6 in control group, the SPPB sores at 3 months was 8.3 ± 0.2 in CR group and 6.9 ± 0.2 in control group (14). To minimize both false positive and false negative errors, the type-I error rate (α) is set at 0.01 instead of 0.05 and the type-II error rate is set at 0.1 instead of 0.2. The sample size is calculated according to the following formula: *n* = 2σ^2^ × *f* (α,β)/(μ_1_-μ_2_)^2^ (19). The sample size of each group was estimated to be 44 per group. Taking approximate a 20% drop-off rate and a 7% missing rate into account, the final sample size was set to 60 per group. Therefore, a total of 120 subjects will be recruited in this study.

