### Data Analysis

Statistical analysis will be conducted using SPSS 25.0 (IBM, Chicago, IL, USA) statistical software. *P* < 0.05 (two-sided) was considered to be statistically significant. Normally distributed continuous variables were presented as mean ± SD and evaluated with paired or unpaired Student's *t* test. Non-normally distributed continuous variables were expressed as median with interquartile range (IQR) and determined by Wilcoxon signed-rank test or Mann-Whitney U test. Categorical variables were recorded as frequency and percentage (*N*, %) and performed by χ^2^ test or Fisher's exact test as appropriate.

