## Discussion

This is a study protocol for a single-center, randomized controlled, single-blind clinical trial to evaluate the efficacy and safety of phase I CR in patients hospitalized in CICU with ADHF. The results of this study will provide reliable evidence for tailored and progressive CR intervention in patients with ADHF.

CR is one of the treatment strategies for HF, which services as one way to reduce the financial burden of HF treatment (24). A recent trial showed CR could improve physical function in patients with ADHF, especially those in NYHA Class II group (14). CICU is usually needed for the patients with ADHF presented with signs of respiratory distress, hypoperfusion, and hemodynamic instability. These patients are at high risk for unexpected in-hospital mortality and re-hospitalization (25). Whether personalized, tailored, and progressive CR intervention is associated with improved QOL and outcomes in patients in CICU with ADHF has not yet been clarified. Thus, evidence on the efficacy and safety of CR intervention is needed in individuals enter the CICU with ADHF.

Tailoring exercise prescription based on the characteristics of patients is necessary for the development of CR in ADHF. Improved SPPB score was related to better prognosis in patients with HF (26). The PEARL study and the REHAB-HF trial showed CR could improve the SPPB score among elderly patients with ADHF (14, 27). However, re-hospitalization rate was not included as a study endpoint in PEARL study. In REHAB-HF trial, reduced re-hospitalization rate was not observed in CR group during the follow-up period. In addition, the majority of CR interventions were conducted in the outpatient setting in REHAB-HF trial. We hypothesize early phase I CR training will increase the SPPB score and reduce the re-hospitalization rate. Additionally, our personalized, tailored and progressive CR program include comprehensive physical fitness interventions. The physical fitness interventions include strength, flexibility, coordination, and balance training. The psychological interventions will be performed by specialized psychological intervention therapists. To achieve the outcomes, strict follow-up procedure will be conducted for 6 months. These measures could promote individualized CR intervention in patients with ADHF.

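### The stated 10% type-II error for SPPB rests on a mainly outpatient trial in non-ICU patients with no argument that its effect transfers, and 44 per group does not deliver 90% power even if it transfers in full

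*Protocol article*

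**What the plan says.** The Sample Size section uses SPPB results from reference 14 and from no other source. It quotes baseline values of 6.0 (SD 2.8) and 6.1 (SD 2.6), and then "the SPPB sores at 3 months was 8.3 ± 0.2 in CR group and 6.9 ± 0.2 in control group (14". It sets the type-II error at 0.1 and says of the other error rate that "the type-I error rate (α) is set at 0.01 instead of 0.05". It arrives at 44 per group, raised to 60 for losses. Data Analysis uses a different threshold: "0.05 (two-sided) was considered to be statistically significant".

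The Introduction identifies reference 14 and says of it: "In REHAB-HF trial, patients admitted to the intensive care unit were excluded". The Discussion adds that "the majority of CR interventions were conducted in the outpatient setting in REHAB-HF trial" and that the benefit was seen "especially those in NYHA Class II group (14".

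For the present trial, the Abstract says "The subjects will receive the CR training for 5 days". Recruitment is in the CICU, and Inclusion Criteria (4) reads "Patients who have New York Heart Association Cardiac Function class III or IV symptoms at admission".

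**The concern.** The Introduction and Discussion use the differences between the two trials to explain why this one is needed. The Sample Size section then plans on the earlier trial's results without mentioning those differences, discounting the effect or arguing that it transfers. A power figure is only as good as the effect behind it, and here the article itself gives reasons to doubt that the effect applies.

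SPPB is a primary outcome, and the section says that the error rates were tightened to limit false negatives as well as false positives. A reader who sees a type-II error of 0.1 may take a non-significant SPPB result as good evidence that rehabilitation in the CICU does not work. If the real power is well below 90%, such a result would be quite likely even when the treatment helps.

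**Working it through.** **Inputs.** All are from Sample Size unless noted.
- Between-group difference at 3 months in the earlier trial: 8.3 − 6.9 = 1.4 points.
- SD: 2.7, midway between the quoted baseline SDs of 2.6 and 2.8. The ± 0.2 at 3 months is far too small to be an SD beside these and reads as a standard error.
- Evaluable patients: 44 per group.
- Alpha: 0.01 in Sample Size, 0.05 two-sided in Data Analysis. Both are shown.

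**Step 1: the article's own figure.** Its formula is n = 2σ² × f(α,β)/(μ₁ − μ₂)². For two-sided 0.01 and 90% power, f = (2.576 + 1.282)² = 14.88.
- Difference 1.4, SD 2.7: 2 × 7.29 × 14.88 / 1.96 = 110.7, so 111 per group (103 with SD 2.6, 120 with SD 2.8).
- SD 0.2 taken at face value: 0.6, so 1 per group.
- Difference 2.3 (the CR arm's own change, 8.3 − 6.0), SD 2.8: 2 × 7.84 × 14.88 / 5.29 = 44.1.

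The quoted between-group difference does not give 44. Of the combinations tried, the closest match at the stated error rates uses the change within the CR arm. The article does not say that this was done. The step from 44 to 60 does reproduce: 44/(0.80 × 0.93) = 59.1, or 44/0.73 = 60.3.

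**Step 2: power if the effect transfers in full.** Two-sample t test, 86 degrees of freedom. Standard error = 2.7 × √(2/44) = 0.576. Noncentrality = 1.4/0.576 = 2.43. Critical values are 1.988 (alpha 0.05) and 2.634 (alpha 0.01). Noncentral t power is 67% and 42%.

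**Step 3: power if only part transfers.** The fractions are assumptions; the document supplies none.

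| Share of 1.4 points | Difference | Power, alpha 0.05 | Power, alpha 0.01 |
|---|---|---|---|
| 100% | 1.40 | 67% | 42% |
| 75% | 1.05 | 44% | 22% |
| 50% | 0.70 | 22% | 8% |

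With SD 2.6 or 2.8 in place of 2.7, the full-transfer row becomes 70% or 64% at 0.05, and 46% or 39% at 0.01. With all 60 per group evaluable (SD 2.7), full transfer gives 80% or 59%, and half gives 29% or 12%.

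**Step 4: difference detectable with 90% power.** With 44 per group and SD 2.7, it is 1.89 points at 0.05 and 2.26 at 0.01. With 60 per group it is 1.61 and 1.93.

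**Step 5: the two trials as the article describes them.**

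| | Earlier trial | Present trial |
|---|---|---|
| Intensive care | excluded | recruited in the CICU |
| Setting | mostly outpatient | 5-day course, in patients hospitalized in the CICU |
| NYHA | benefit especially in class II | class III or IV at admission |

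**The case against.** Power is always conditional on an assumed effect. Planning on a randomized trial in ADHF with the same endpoint is ordinary practice, and the article discloses the differences openly. It also says that it aims to explore efficacy and that later studies must confirm it, which makes the feared over-reading of a null result less certain. This stands as far as it goes. The choice of source is defensible; stating 90% power on it without qualification is not.

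Several stronger readings are tempting, and the document does not support them.
- **That the change of population and setting takes power from 90% to the figures in the lower rows.** Much of the gap is already there at full transfer. At alpha 0.01, 90% falls to 42% before any discount, and a 25% loss of effect removes only about 20 points more. Likewise, the detectable difference exceeds 1.4 points even with perfect transfer, so that comparison says nothing about setting.
- **That the effect here must be smaller.** No passage gives an SPPB effect for a 5-day CICU course. The 75% and 50% rows are illustrations.
- **That the earlier programme was longer, or that patients here get no outpatient rehabilitation.** The article does not give the earlier programme's duration; 3 months is a measurement time. Table 2 lists participation in phase II rehabilitation as a follow-up item.
- **That the NYHA classes do not overlap.** Class III or IV applies at admission. Patients must then be stable for 24 hours, and Table 1 allows class II from level 4 upward. Benefit especially in class II also does not mean little benefit in other classes.

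It is fair to add that the SD of 2.7 comes from the same earlier trial, so the detectable difference inherits part of the transfer problem.

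**Conclusion.** The concern holds in a limited form. The unqualified type-II error of 0.1 is not supported, for two separate reasons. First, the planning effect comes from a trial that the article itself describes as different in care setting and patients, and no argument for transfer is offered; the resulting loss is unknown. Second, even with full transfer of the 1.4-point difference, 44 evaluable per group gives about 67% power at two-sided 0.05 or 42% at 0.01. These figures assume an SD of 2.7 and a two-sample t test. The lower figures (44% and 22% at 0.05; 22% and 8% at 0.01) also assume 75% or 50% transfer and should be cited only with that label.

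**What to change.** Keep 120 patients and rewrite the justification in Sample Size:

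1. Drop the unqualified type-II error of 0.1.
2. State the difference detectable with 90% power at the alpha that the analysis will use: about 1.9 points at 0.05 or 2.3 at 0.01, with 44 evaluable per group. Say that the SD of 2.7 is taken from the earlier trial's baseline. One alpha must be chosen, since Sample Size and Data Analysis now differ.
3. Give power at 1.4, 1.05 and 0.7 points beside it: 67%, 44% and 22% at 0.05, or 42%, 22% and 8% at 0.01.
4. Say that the planning effect comes from a mainly outpatient programme in non-ICU patients and that its transfer to this setting is not established. Do not call that programme longer unless a source is given.
5. State that a non-significant SPPB result will be read from the confidence interval and not as absence of benefit. On the same inputs the 95% interval would be about ± 1.988 × 0.576 = ± 1.1 points, so an estimate of zero would not exclude a benefit of 1.05 points.

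The cost is wording in one paragraph and no further patients. The downside is that the stated power becomes less favourable.

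### The 44 per group does not follow from the quoted between-group SPPB difference of 1.4 points, for which power is well below the stated 90%

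*Protocol article*

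**What the plan says.** The Sample Size section rests on SPPB results from one earlier trial. For baseline it reports that "the baseline SPPB sores was 6.0 ± 2.8 in CR group and 6.1 ± 2.6 in control group". For follow-up it reports that "the SPPB sores at 3 months was 8.3 ± 0.2 in CR group and 6.9 ± 0.2 in control group". No ± term is labelled.

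On error rates, "the type-I error rate (α) is set at 0.01 instead of 0.05" and "the type-II error rate is set at 0.1 instead of 0.2", with the aim of limiting both kinds of error. The formula is the standard one for two independent means: n per group equals twice the variance, times a function of alpha and beta, divided by the squared difference in means. The result is "The sample size of each group was estimated to be 44 per group", raised to 60 per group for 20% drop-off and 7% missing data. The section does not say which two means or which SD were entered.

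The Study Design section confirms that patients are "randomly assigned to the two groups with a 1:1 ratio". The Data Analysis section plans t tests (or rank tests) at a two-sided 0.05.

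**The concern.** The formula compares two groups, so the difference entered should be a difference between groups. The follow-up means quoted differ by 1.4 points. With SDs near 2.7 that is about half an SD, and 44 per group is far too few for 90% power at alpha 0.01.

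SPPB is one of the two primary outcomes and the only one used for sizing. If the power claim is wrong, a null SPPB result could be read as evidence from a 90%-powered trial when it is not. The paragraph also presents its error rates as stricter than usual, which makes that misreading more likely.

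**Working it through.** **Inputs.** From Sample Size: alpha 0.01, beta 0.1, baseline SDs 2.8 (CR) and 2.6 (control), baseline means 6.0 and 6.1, 3-month means 8.3 and 6.9. From Data Analysis: two-sided testing. Assumption: no patient-level SD at 3 months is given, so the baseline range 2.6 to 2.8 is carried forward.

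**Formula.** n per group = 2 × SD² × f / difference², with f = (2.576 + 1.282)² = 14.88.

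**Reproducing 44.** Of the combinations of quoted means and SDs tried under the stated alpha and beta, the closest is SD 2.8 with 8.3 − 6.0 = 2.3:

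2 × 2.8² × 14.88 / 2.3² = 44.1

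This is the CR arm's 3-month mean minus its own baseline. It is not a treatment effect, because the control arm also rose, from 6.1 to 6.9. Another near match is 8.3 − 6.1 = 2.2 with SD 2.7, giving 44.8; that sets CR follow-up against control baseline and is not a treatment effect either.

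The attrition step is sound: 44 / (0.80 × 0.93) = 59.1, so 60.

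**Between-group difference, 8.3 − 6.9 = 1.4.**

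- SD 2.8: 2 × 2.8² × 14.88 / 1.4² = 119.0, so 120 per group
- SD 2.7: 110.7, so 111
- SD 2.6: 102.6, so 103

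**Other readings tried.**

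- Difference in changes, 2.3 − 0.8 = 1.5, with the same SDs: 89.4 to 103.7 per group.
- One-sided alpha 0.01 with 1.4: 89.8 to 104.1 per group.
- ±0.2 entered as the SD with 1.4: 0.6 per group, so it cannot be a patient-level SD.
- SD needed for 44 with 1.4: √(44 × 1.4² / (2 × 14.88)) = 1.70. No figure in the section supplies this.

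**Power for a true difference of 1.4** (two-sided t test, noncentral t with noncentrality 1.4 / (SD × √(2/n))):

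| Evaluable per group | Alpha | SD 2.8 | SD 2.7 | SD 2.6 |
|---|---|---|---|---|
| 44 | 0.01 | 39% | 42% | 46% |
| 44 | 0.05 | 64% | 67% | 70% |
| 60 | 0.01 | 55% | 59% | 63% |
| 60 | 0.05 | 78% | 80% | 83% |

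**Difference for which 44 per group has 90% power at alpha 0.01**, from the protocol's formula: SD × √(2 × 14.88 / 44) = 2.14 (SD 2.6), 2.22 (SD 2.7) or 2.30 (SD 2.8).

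**The case against.** Four points can be made for the plan.

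- **The follow-up SD is unknown.** This stands as a caveat: every figure for 1.4 points assumes that the baseline SD carries over. But the SD would have to fall to about 1.70 to rescue 44, and nothing in the section suggests that.
- **Baseline adjustment would cut the variance.** It could, but a baseline-to-follow-up correlation of about 0.76 to 0.79 would be needed for 44 to suffice. The formula has no such term, and the stated analysis is an unadjusted t test.
- **The test will be run at 0.05, not 0.01.** This also stands and limits the consequence. A reader might infer that the trial is more likely than not to miss the effect it cites. That holds only at alpha 0.01 with about 44 evaluable per group. At the Data Analysis threshold power is 64-70%, and 78-83% if all 60 are evaluable. Both ranges are below 90%, but above one half.
- **The origin of 44 is a reconstruction.** Correct. A reader might infer that the CR arm's before-after change was certainly used. The document does not say so, and 2.2 with SD 2.7 also comes close. The finding does not depend on how 44 was reached, only on its not following from 1.4.

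It is also tempting to declare the ±0.2 a standard error. The documents show only that it cannot be a patient-level SD; whether it is a raw or an adjusted standard error, or a copying slip, cannot be settled from them.

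**Conclusion.** The point holds. Under the section's own formula, alpha and beta, with two-sided testing and SDs of 2.6 to 2.8 assumed at follow-up, the quoted between-group difference of 1.4 calls for 103 to 120 evaluable patients per group, not 44. That is about 2.3 to 2.7 times the stated number. With 44 per group, power for that difference is about half the stated 90% at alpha 0.01, and roughly two thirds to 70% at alpha 0.05. The section names no larger target difference that would justify 44. The error is in the 44 itself; the step from 44 to 60 is correct.

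**What to change.** Keep 120 patients and correct the Sample Size paragraph:

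1. State which difference and which SD were actually entered to obtain 44.
2. Check what ±0.2 is against the cited trial and label every ± term.
3. State that 44 evaluable per group gives 90% power at two-sided alpha 0.01 only for a between-group difference of about 2.1 to 2.3 points (SD 2.6 to 2.8).
4. Report the power for 1.4 points at both alphas in the protocol: about 39-46% at 0.01 and 64-70% at 0.05 with 44 evaluable, or 55-63% and 78-83% if all 60 are evaluable, noting that the baseline SD is assumed at follow-up.

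The cost is one reworded paragraph and a less favourable power statement; no extra patients are needed. The rewording makes the claim accurate but does not restore 90% power for 1.4 points. Under the plan's own error rates and attrition that would take 103 / 0.744 to 120 / 0.744 (0.744 = 0.80 × 0.93), or 139 to 162 per group.
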